#### Inclusion criteria

The inclusion criteria for the study will be participants aged between 18 and 65 years; both sexes; complaint of low back pain lasting more than 3 months; magnetic resonance imaging findings of lumbar disc degeneration (LDD) performed less than 6 months before inclusion in the study; indication for open surgical treatment with isolated microdiscectomy or associated with lumbar arthrodesis; failure of conservative treatment for at least 6 weeks and/or progressive neurological deficit; agreement to follow all phases of the clinical investigation, having signed the informed consent form (ICF) for participation in the study.

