### Participant allocation

The participants will be operated by the same surgical team, and the surgical technique will be posterior discectomy followed by arthrodesis of the approached segment.

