### Confounding variables

As some of this information may change during the study, the data obtained at the time of inclusion in the study will be considered. Below are the confounding variables to be analyzed:

AgeSexEducationLeave of absenceAlcohol consumption
None or sporadically (< 1 dose/day)Mild (1–2 doses/day)Moderate/High (≥ 3 doses/day)Smoking
Non-smokerSmokerEx-smokerBody mass index
Underweight (< 18.5 Kg/m^2^)Normal (18.5–25 Kg/m^2^)Overweight (25–30 Kg/m^2^)Obese (> 30 Kg/m^2^)Physical activity practice
Sedentary (not performing physical activity for at least 10 continuous minutes during the week)Active (vigorous activities for three or more days/week and for 20 min or more per session; or moderate activity or walking for five or more days/week and for 30 min or more per session; or any activity added together 5 or more days/week and 150 min or more/week)Very active (vigorous activity for five or more days/week and 30 min or more per session; vigorous activity for three or more days/week and 20 min or more per session, more moderate activity and/or walking for five or more days/week and for 30 min or more per session)Use of oral steroids up to 3 months before surgeryDiabetes

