## Statistical planning

### Sample size calculation

Considering the main outcome proposed, the identification of disc colonization by *C*. *acnes*, the minimum sample size (*n*) for the population of interest will be 96 participants, according to the calculation described by Medronho et al., [59] using a confidence interval of 95% and a maximum margin of error of 10%.

The ideal sample size for analysis of secondary outcomes will depend on the incidence of the main outcome. If it is too low, an increase in the number of patients included will be performed with the inclusion of more blocks of participants. In order to have a more accurate dimension, the sample size calculation will be revised as soon as we reach half of the initially planned sample size.

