### Statistical analysis methodology

The database will be analyzed using the SPSS software, version 22.0, and R software, version 4.0.2. Descriptive analysis will be performed by charts and descriptive statistics. The inferential analysis will consider a maximum significance level of 5%. The chi-square test or Fisher’s exact test will be used for inferential analysis of the distributions of categorical variables. The odds ratio (OR) will be the measure used to estimate risk. The OR’s significance will be evaluated by the OR’s asymptotic confidence interval. The hypothesis of normality will be verified by the Kolmogorov–Smirnov and Shapiro–Wilk tests. Student’s t-test or Mann-Whitney test will be used in the comparison of the two independent groups. More than two independent groups will be compared by the ANOVA or by the Kruskal–Wallis test. Two repeated measures in different assessments will be compared by the paired Student’s t-test or by the Wilcoxon’s signed-rank test. More than two repeated measures will be compared by the ANOVA for repeated measures, or by the Friedman’s test.

The identification of an optimal cutoff point for the marker associated with an outcome will be established through the analysis of the receiver operating characteristic (ROC) curve. The performance will be evaluated by the area under the ROC curve (AUC), and the significance of the AUC will be evaluated by the test that judges the null hypothesis that AUC is equal to 0.5. In addition to the significance test, the asymptotic confidence interval for the AUC will be obtained.

Analysis of the association between two quantitative variables will be visualized by scatter plots and quantified by the Pearson correlation coefficient, in the case of normal distributions, or by the Spearman’s correlation coefficient, if normal distribution is not verified in at least one of the variables. The significance of the correlation coefficient will be evaluated by the correlation coefficient test.

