Linear or non-linear regression models will be proposed to explain the relationship between the clinical–radiological variables of the patient and the quantitative outcome variables (colonization and multiomic profile). For the variable colonization (binary), logistic regression models will be proposed. Regression model parameters will be estimated by the maximum likelihood method, and the forward Wald method will be used to choose the variables. The goodness of fit of the model will be analyzed by adherence statistics, residual analysis, and verification of theoretical assumptions of the model.

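### No stated model has pain, disability or quality of life as the outcome with colonization and the listed confounders as covariates, although the protocol says confounding is controlled

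*Protocol article*

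**What the plan says.** All references are to the protocol article.

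- **Outcomes and timing.** Secondary outcomes names VNS, EQ-5D and ODI, and sets quality of life against colonization status and Modic changes. Questionnaires gives the times: recruitment and 1, 3 and 6 months after surgery.
- **Confounding.** Justifications presents control of confounding as a feature of the protocol. Confounding variables says "Below are the confounding variables to be analyzed" and lists age, sex, education, leave of absence, alcohol, smoking, body mass index, physical activity, oral steroids and diabetes.
- **Tests.** Statistical analysis methodology sorts tests by type of data. For two groups, Student's t-"test or Mann-Whitney test will be used in the comparison of the two independent groups". Two repeated measures get a paired t-test or Wilcoxon test. For longer series, "More than two repeated measures will be compared by the ANOVA for repeated measures", or Friedman's test. No covariate is mentioned for any of these.
- **Regression.** The same section relates clinical and radiological variables to "the quantitative outcome variables (colonization and multiomic profile"). Colonization gets logistic regression, and variables are chosen by forward Wald.
- **Withdrawal.** Withdrawal of a study participant removes patients for, among other reasons, loss of follow-up, intense pain or signs of infection. It says that data gathered up to that point enter the final analysis.
- **Procedure.** Inclusion criteria has "indication for open surgical treatment with isolated microdiscectomy or associated with lumbar arthrodesis". Participant allocation has "the surgical technique will be posterior discectomy followed by arthrodesis of the approached segment".

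**The concern.** Colonization is observed, not assigned. Colonized and non-colonized patients may differ in age, smoking, body mass index, activity or diabetes, and each of these may also bear on pain and function. A t-test or Mann-Whitney comparison of scores mixes those differences with any association with colonization. Friedman's test and the paired tests have no between-group factor, so they cannot compare the two groups at all.

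The models that could adjust have the other orientation: they explain colonization, or the multiomic profile, from the clinical variables. They do not yield an adjusted difference in pain, disability or quality of life. Forward Wald also leaves it to the data whether any listed confounder is kept.

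At stake is whether the article can report a confounder-adjusted difference in the three patient-reported outcomes, and whether the visits of patients who later leave the study are used.

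**Working it through.** **1. The plan's own figure.** Sample size calculation says "the minimum sample size (*n*) for the population of interest will be 96 participants", from a 95% interval and a 10% margin. With p = 0.5 (assumed, not stated), n = 1.96² × 0.5 × 0.5 / 0.10² = 96.04. This reproduces 96. The recruitment target of 120 corresponds to 20% loss: 120 × (1 − 0.20) = 96. This is a precision calculation for the colonization proportion and does not depend on how the scores are analysed.

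**2. Stated methods set side by side.**

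| Stated method | Score as outcome? | Colonization as a factor? | Confounders? |
|---|---|---|---|
| t-test / Mann-Whitney | can be | yes | no |
| ANOVA / Kruskal-Wallis | can be | yes | none stated |
| Paired t / Wilcoxon | can be | no | no |
| Repeated-measures ANOVA | can be | possible, not stated | none stated |
| Friedman | can be | no | no |
| Regression models | no: outcome is colonization or multiomic profile | it is the outcome | possible, by forward Wald |

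No row has a score as outcome together with colonization and the listed confounders.

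**3. What an unadjusted comparison could cost (assumed inputs).** The documents give no SD or correlation. Take a standardized covariate that differs by d SD between groups and correlates r with the score, and no true effect. The expected spurious difference is r × d. With N = 96 and 46% colonized (the culture-positive share for anaerobes in a discectomy study cited in the Introduction), the groups are 44.2 and 51.8, and the standard error in SD units is √(1/51.8 + 1/44.2) = 0.205.

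- d = 0.4, r = 0.5: shift 0.20 SD, 0.20/0.205 = 0.98 standard errors, two-sided type I error about 16%.
- d = 0.2, r = 0.3: shift 0.06 SD, about 6%.
- d = 0.5, r = 0.7: shift 0.35 SD, about 40%.

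The upper values suit a strong predictor such as the recruitment score. A single demographic variable would usually do less.

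**4. Complete rows (assumed inputs).** If a share m misses each of three follow-up visits independently, 1 − (1 − m)³ have an incomplete row: 14.3% at m = 5% and 27.1% at m = 10%. If the same people miss every visit, the loss is only 5% to 10%. In either case, dropping those rows sets aside the earlier visits that the withdrawal section says will be included. Because intense pain is a removal reason, the loss may be related to the outcome.

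**5. How much model the data can carry.** At the 3.4% culture-positive rate in another cited study (a rate for discs, applied here to patients), 96 × 0.034 = 3.3, so about 3 colonized patients. At 46% there would be about 44.

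**The case against.** The methodology section is a generic menu that ties no test to VNS, ODI or EQ-5D by name, and a condensed article may leave that allocation to an analysis plan that is not shown. That stands, so the allocation is an inference. It does not remove the point: the article itself chose the dependent variables of its regressions, and the scores are not among them.

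A reader might infer more than the text supports:

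- **That baselines never enter.** Recruitment is one of four measurement times, so it can be a time level in repeated-measures ANOVA or enter a paired test. A change score is not excluded, and the 30% pain criterion is defined against baseline. What is absent is baseline as a covariate.
- **That no stated method could test whether change differs by colonization.** Repeated-measures ANOVA can carry a group factor and a group-by-time term. Only Friedman and the paired tests cannot.
- **That the confounders are used nowhere.** They may be candidates in the colonization models, which can give an adjusted association in the other direction.
- **That complete-case deletion is planned.** It is not stated. It follows only if the named tests are run conventionally.
- **That procedure type is an omitted confounder.** If every patient has the same operation it cannot confound. If operations vary, it confounds only if it is also related to colonization, which nothing in the document shows.

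A further objection concerns the remedy. The study hypothesis links colonization to pain, so the preoperative score may partly result from colonization, and conditioning on it may remove part of the association sought. This stands, and it is why baseline adjustment belongs in a sensitivity analysis.

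**Conclusion.** The point holds in this form: the protocol says confounding is controlled but states no analysis that does so with pain, disability or quality of life as the outcome. The conventional form of its repeated-measures tests also sits badly with its promise to use data gathered before withdrawal.

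It concerns secondary outcomes only. The incidence of colonization and n = 96 are untouched. The size cannot be derived from the documents. The 6% to 40% type I error range and the 5% to 27% incomplete rows are illustrations under assumed imbalance, correlation and missingness. The change is worth making before the scores are analysed by colonization status.

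**What to change.** For each of VNS, ODI and EQ-5D, state one linear mixed model for the scores at recruitment and months 1, 3 and 6, using all available visits. Include colonization, visit, colonization × visit and a short confounder set from the protocol's list, fixed in advance and forced in rather than chosen by forward Wald. Report the adjusted group difference at recruitment and the difference in change at each later visit.

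As a sensitivity analysis, model the postoperative scores with the recruitment score as a covariate. Keep the simple tests as descriptive.

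State how the covariates will be cut back if few patients are colonized; with about 3 of 96, the full model would not be usefully estimable. This is the small downside. The mixed model also does not cure loss that depends on pain never recorded, so withdrawal reasons should be tabulated by group.

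Reconcile Inclusion criteria and Participant allocation on the surgical procedure, and add procedure type as a covariate only if it varies.

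The cost is wording: the scores and confounders are already collected, and the planned R software fits the model.

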## Introduction

LBP is a common complaint in the general population, and its incidence is about five times higher in patients with LDD and Modic endplate changes [1, 2]. The link between these findings and the isolation of low virulence pathogens in LIVD has already been described in several studies, generating a lot of interest in the topic and promoting the bacterial hypothesis of LDD [3–14].

Albert et al. reported 46% of positive cultures for anaerobes in 61 patients undergoing lumbar discectomy, of which 80% had Modic type 1 changes [15]. Other studies corroborate these findings, with high identification rates for *Cutibacterium acnes*, an anaerobic and aerotolerant pathogen that is bacillus-shaped, stained by the Gram method, pleomorphic, non-spore-forming, and a biofilm producer [11, 16–20]. Rollason et al. isolated strains of this bacterium from the LIVD of 64 patients, revealing the presence of genotypic profiles distinct from those found in the skin, suggesting that specific variants would be related to LBP [21].

Other authors believe that the presence of this pathogen in the LIVD of asymptomatic patients is due to contamination of the specimens during sampling and/or sample treatment in the laboratory environment. Carricajo et al. found positive cultures for *C*. *acnes* in only 3.4% of the discs from 54 patients, defending the possibility of contamination [22]. Rigal et al. also analyzed LIVD from 313 patients who underwent video-assisted retroperitoneal discectomy, with positive cultures for only six patients [23].

These marked divergences in microbiological results cast doubt on the bacterial hypothesis of LDD and, consequently, raise questions about the possibility of anaerobic pathogens acting as triggers or amplifiers of LBP. Urquhart et al. conducted a systematic review of the literature on the subject and concluded that there is evidence correlating the *C*. *acnes* isolation with Modic type 1 changes and LBP, but there is a lack of studies producing substantial and irrefutable evidence [24].

Despite the fact that considerable effort has already been expended in determining the presence of *C*. *acnes* in LIVD, there are still no standard isolation protocols for this pathogen from this clinical specimen. Furthermore, prior to the preparation of this manuscript, studies have shown no consistency in the collection and analysis techniques used, making comparison and reproducibility of results difficult.

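### If few discs are colonized, an untransformed asymptotic confidence interval for the AUC is too narrow and often passes 1, and the plan names no small-sample alternative

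*Protocol article*

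**What the plan says.** Under Statistical analysis methodology, the ROC curve serves "The identification of an optimal cutoff point for the marker associated with an outcome". The AUC is the performance measure, and two inferences are attached to it. The first is a test: "the significance of the AUC will be evaluated by the test that judges the null hypothesis that AUC is equal to 0.5". The second is an interval: "In addition to the significance test, the asymptotic confidence interval for the AUC will be obtained". The outcome, the variance estimator and the scale are not named.

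Host multiomic characteristics looks for blood profiles linked to the pathogen's presence in the disc. This makes colonization a plausible ROC outcome.

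Under Sample size calculation, the minimum "for the population of interest will be 96 participants"; Patient and public involvement sets 120 inclusions to reach it. On the secondary analyses: "The ideal sample size for analysis of secondary outcomes will depend on the incidence of the main outcome". Participants are to be added if incidence proves too low, with a review at half the planned sample. No threshold or target number of colonized participants is given.

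The Introduction cites widely differing culture rates: 46% positive for anaerobes in one series, 3.4% of discs in another, and a series of 313 patients "with positive cultures for only six patients".

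**The concern.** The precision of an AUC is governed mainly by the smaller of the two outcome groups. With two or three colonized participants, the nonparametric standard error rests on two or three values. A symmetric interval of estimate ± 1.96 standard errors also ignores the bound at 1. It can therefore be far too narrow, run past 1, or shrink to zero width when the marker separates the groups completely. This happens even for one marker fixed in advance, so it is separate from multiplicity and from cutoff selection.

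The same section provides small-sample or rank-based alternatives for other analyses (Fisher's exact, Mann-Whitney, Wilcoxon, Spearman), but none for the AUC interval. At stake is how the molecular marker's performance is reported: a 95% interval could miss the true AUC far more often than one time in twenty.

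**Working it through.** **The plan's own figure.** The article states no coverage or precision for the AUC. Its sample size reproduces: 1.96² × 0.5 × 0.5 / 0.10² = 96.04, so 96 (a proportion of 0.5 is assumed).

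**Colonized counts at the cited rates.**
- 6/313 = 1.9%: 1.8 of 96, 2.3 of 120.
- 3.4%: 3.3 of 96, 4.1 of 120.
- 46%: 44 of 96.

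The three rates have different bases (patients with any positive culture, discs, anaerobes), so the counts only indicate scale.

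**Formulas.** Let m be the colonized, n the non-colonized and A the AUC.
- Hanley-McNeil variance: [A(1−A) + (m−1)(Q1−A²) + (n−1)(Q2−A²)]/(mn), with Q1 = A/(2−A) and Q2 = 2A²/(1+A).
- Untransformed interval: A ± 1.96·SE.
- Logit interval: logit(A) ± 1.96·SE/[A(1−A)], transformed back.

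**Example, m = 3, n = 93, observed A = 0.8.**
- Q1 = 0.667, Q2 = 0.711, A² = 0.64.
- Variance = (0.16 + 2 × 0.0267 + 92 × 0.0711)/279 = 0.0242, so SE = 0.156.
- Untransformed: 0.8 ± 0.305 = 0.495 to 1.105, which is past 1.
- Logit: 1.386 ± 1.96 × 0.973 = −0.520 to 3.292, which is 0.373 to 0.964.

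**Example, m = 44, n = 52, A = 0.8.** SE = 0.046. The untransformed interval is 0.709 to 0.891 and the logit interval 0.694 to 0.876; both have width 0.18.

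**Coverage by simulation.** One pre-specified normal marker with equal variances was used, with 20,000 runs per cell (5,000 at m = 44). The true AUC is an assumption, because the article gives none. Each cell shows AUC 0.8 / 0.9.

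| Colonized of N | DeLong coverage | Hanley-McNeil coverage | DeLong limit above 1 | Hanley-McNeil limit above 1 |
|---|---|---|---|---|
| 2 of 96 | 64% / 58% | 87% / 85% | 68% / 76% | 87% / 89% |
| 3 of 96 | 74% / 68% | 91% / 88% | 65% / 84% | 86% / 95% |
| 4 of 120 | 79% / 72% | 92% / 91% | 52% / 79% | 80% / 97% |
| 10 of 96 | 89% / 84% | 96% / 96% | 7% / 40% | 29% / 86% |
| 44 of 96 | 94% / 92% | 95% / 95% | 0% / 0.3% | 0% / 2% |

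Separate runs agreed to within about one percentage point; the ranges quoted elsewhere span the runs.

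**Alternatives.** The logit-scale Hanley-McNeil interval covered 96% to 99% at AUC 0.8 and 0.9 for every m from 2 to 44, and about 93% in its worst setting (m = 2, AUC 0.5). A score-type interval covered 94% to 97% at m = 2 to 4. Putting DeLong on the logit scale is not enough: it covered 73% to 75% at m = 2 and 79% to 86% at m = 3.

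**Too few cases altogether.** At 1.9% and N = 96, the chance of no colonized participant is 0.981⁹⁶ ≈ 16%, and of none or one about 45% (16% at 3.4%). The DeLong standard error cannot then be computed.

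**The case against.** The strongest reply is that the article says only asymptotic. An untransformed interval and the DeLong error are readings of that word, and a logit-scale interval is asymptotic too. The analysis plan, not shown here, may settle the choice. This stands as a limit on the claim: one cannot say that the plan prescribes the worst variant. But the wording permits estimators that differ by up to 28 points in coverage (58% against 85% at 2 colonized, AUC 0.9), and a better rule can be named at almost no cost.

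Second, the low rates are the contrary view in the Introduction, not planning assumptions, and participants will be added if incidence is too low. This stands in part. No threshold is set, and expecting even 10 cases takes 10/0.034 ≈ 294 participants, or 10/(6/313) ≈ 522. At 10 cases DeLong still covers only 84% to 89%.

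Third, the ROC outcome may be something other than colonization, and these counts would then not apply. This stands as a condition.

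A reader might also infer that a useless marker would be declared significant too often. With 2 or 3 colonized, the DeLong interval excludes 0.5 in about 31% and 20% of samples when the true AUC is 0.5, and Hanley-McNeil in about 17% and 12%. The article does not support that inference, because significance is judged by a separate test. The interval could contradict that test, but its exclusion rate is not the test's error rate.

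**Conclusion.** The concern holds conditionally. If the ROC outcome is colonization, incidence is near the low cited rates and the interval is untransformed, a nominal 95% interval covers about 57% to 80% (DeLong) or about 85% to 93% (Hanley-McNeil) at a true AUC of 0.8 to 0.9, and its upper limit exceeds 1 in most samples. With 10 colonized, the coverage shortfall remains for DeLong only, although at AUC 0.9 both limits still often pass 1. With 44 of 96 colonized, coverage is 92% to 95% and nothing material is wrong.

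The stronger reading, that the planned interval fails across the colonization rates the article cites, is not supported: it fails at the two low rates and not at 46%. The figures rest on a normal marker with equal variances and an assumed AUC. The analysis is secondary and the primary estimate of colonization is unaffected, so the change is advisable rather than essential.

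**What to change.** Replace the sentence on the AUC interval with one that names a method suited to few cases. Either a logit-scale interval with the Hanley-McNeil variance and a continuity correction when the estimated AUC is 0 or 1, or a score-type interval, would serve. Test AUC = 0.5 by the exact Mann-Whitney test when the smaller group is small; in simulation it rejected a useless marker 4% to 5% of the time. State the ROC outcome and a minimum number of cases below which no ROC analysis is reported.

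Coverage is then about 93% to 99%, with limits inside 0 to 1. The cost is one sentence of wording, slight conservatism, and wider intervals when few are colonized: at 3 colonized and AUC 0.8, the median width is about 0.60 instead of 0.35 to 0.38. With 2 colonized and AUC 0.9 it is nearly 0.8, so no formula makes that analysis informative. Near 44 colonized the width is essentially unchanged, at 0.18.

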### Patient and public involvement

Participant eligibility will be evaluated by the study researchers through a clinical interview and imaging exams evaluation, according to the participants’ interest and availability to participate in the study. If the patient agrees to take part in the study, the predetermined selection criteria will be used to evaluate them. The researchers will explain the details of the study and conduct a joint reading of the ICF. Questions about the study objectives, risks and benefits, stages, and research confidentiality will be answered. A patient will only participate upon signing the ICF at this stage of the research. A copy of this document will be given to the participant, another to the responsible researcher, and a third will be attached to the medical record. After signing the consent form, the patient will undergo an evaluation for demographic and clinical data collection and the forms developed for this purpose will be completed. If the patient is unable to read and sign the written consent form, researchers will verbally explain the study details and the patient will orally provide consent in the presence of a witness who will sign the consent form. The recruitment of participants will take place over a 6-month period, until 120 individuals are included, aiming at a minimum number of 96 collections.

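### Forward Wald selection in the colonization model can drop the confounders the protocol promises to control, with at most about 3 to 4 colonized patients per candidate parameter at the planned 96 to 120 patients

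*Protocol article*

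**What the plan says.** The section Statistical analysis methodology plans logistic regression for colonization, fitted by maximum likelihood, with clinical and radiological variables as predictors. It then fixes the selection rule: "the forward Wald method will be used to choose the variables". No variable is exempt, and no entry or removal threshold is given. For odds ratios, "significance will be evaluated by the OR’s asymptotic confidence interval". The same section allows Fisher's exact test for categorical tables.

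The section Confounding variables lists ten variables to be analysed, and Justifications presents control of confounding as a strength of the design. The second of the further objectives is the association of the pathogen with the clinical picture and with Modic type 1 changes, so these odds ratios answer a stated objective.

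The minimum sample "for the population of interest will be 96 participants", calculated "using a confidence interval of 95% and a maximum margin of error of 10" per cent. Recruitment runs "until 120 individuals are included, aiming at a minimum number of 96 collections". The sample may grow if incidence is too low: "the sample size calculation will be revised as soon as we reach half of the initially planned sample size".

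The lowest physical-activity level is defined as "Sedentary (not performing physical activity for at least 10 continuous minutes during the week"; the next level is Active.

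**The concern.** A variable named in advance as a confounder should stay in an association model because of what is known about it. Under forward Wald it stays only if its own p-value is small. That rule is built for prediction. It does not deliver the promised control of confounding, and intervals computed afterwards make no allowance for the selection.

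Because colonization is the outcome and the radiological variables are predictors, Modic type 1 is itself open to selection. The odds ratio the reader most wants would then be reported mainly when it happens to be large.

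The sample was sized for the precision of one proportion, so nothing guarantees enough colonized patients for a model of this size. If few are colonized, maximum likelihood and asymptotic intervals may fail altogether.

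**Working it through.** **The plan's own figure.** n = z² × p(1 − p) / d² with z = 1.96, p = 0.5 (assumed; the protocol states no expected proportion) and d = 0.10 gives 3.84 × 0.25 / 0.01 = 96.04. This reproduces the 96. The 120 inclusions match a 20% loss: 96 / 0.80 = 120.

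**Candidate parameters**, counted as levels minus one: age 1, sex 1, education at least 1, leave of absence 1, alcohol 2, smoking 2, body mass index 3, physical activity 2, oral steroids 1, diabetes 1. The total is at least 15.

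**Colonized patients.** The protocol assumes no rate. The Introduction cites "46% of positive cultures for anaerobes in 61 patients undergoing lumbar discectomy" as the highest (any anaerobe, not *C. acnes* alone), and 3.4% and 6/313 = 1.9% as low values.

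| Rate | N = 96 | per parameter | N = 120 | per parameter |
|---|---|---|---|---|
| 46% | 44.2 | 2.9 | 55.2 | 3.7 |
| 3.4% | 3.3 | 0.2 | 4.1 | 0.3 |
| 1.9% | 1.8 | 0.1 | 2.3 | 0.2 |

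The smaller outcome group cannot exceed half the sample: 48 (3.2 per parameter) or 60 (4.0 per parameter).

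**Simulation of the selection rule.** The assumptions are: entry at p < 0.05, removal at p > 0.10, multi-level factors entered as blocks, about 45% colonized, and Modic type 1 in about 40%. Three of the ten confounders are real, with odds ratio 1.5 or 2.0 for both Modic type 1 and colonization. There were 1,000 runs per setting, and 1,500 with no true predictor.

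- No true predictor: at least one variable is kept in 40% of runs. The independence approximation agrees: 1 − 0.95^10 = 40.1%.
- Three true confounders, N = 96: at least one is dropped in 88 to 99% of runs (on average 1.5 to 2.3 of the three). At least one of the seven noise variables is kept in 29 to 33%; compare 1 − 0.95^7 = 30.2%.
- Modic type 1 forced in, N = 96: nominal 95% intervals cover 90 to 94%.
- Modic type 1 left to selection, true odds ratio 2, N = 96: it enters in 42 to 43% of runs. When it enters, its geometric mean odds ratio is 3.7 to 4.0 and coverage is 81 to 87%.
- N = 120: a confounder is dropped in 83 to 99% of runs and noise is kept in 30 to 34%. Coverage is 90 to 93% (forced) and 84 to 89% (selected, true odds ratio 2).

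Monte Carlo standard error is about 1 point for forced coverage, √(0.9 × 0.1 / 1000), and about 1.7 points for coverage when selected, √(0.85 × 0.15 / 425).

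**Sparse tables.** Let q be the share with Modic type 1. With k colonized patients, the chance that all or none of them have it is (1 − q)^k + q^k. For k = 3 and an assumed q = 0.30 this is 0.343 + 0.027 = 0.37. Over k = 2 to 4 it runs from 0.58 to 0.25; with q = 0.40 it runs from 0.52 to 0.16. The odds ratio is then zero or infinite and has no usual asymptotic interval.

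**Physical activity.** Someone who walks 20 minutes on three days a week (60 minutes) is not Sedentary as defined. That person also has no vigorous activity, fewer than five active days and under 150 minutes, so is neither Active nor Very active.

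**The case against.** Several limits on this point are fair.

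- A reader might take 44 as the most colonized patients the study can have. It is 46% of the minimum sample; 120 inclusions give about 55, and the protocol allows more if incidence is low. This stands. However, the increase has no stated size or trigger, and even an even split of 120 gives only 4 per parameter.
- The protocol never says that the confounder list is the pool for selection; it names clinical and radiological predictors. That link is an inference. No other way of adjusting is described, though, and adding Modic, Pfirrmann, pain or disability variables would only raise the count.
- A reader might infer that confounders are certain to be lost, that noise is certain to enter, or that every interval is invalid. The figures rest on assumed effects and thresholds and show likelihoods only. Treating the 15 parameters as separate candidates would put noise selection at 1 − 0.95^15 = 54%; with ten variables entered as blocks it is about 30 to 40%. Under-coverage is mild when the exposure is forced in, and 94% is hardly distinguishable from 95% at this simulation size.
- Fisher's test already covers testing in sparse tables. That is so; the weakness is in the interval by which the odds ratio is judged.
- The activity gap is a data-definition matter separate from selection, and the collection form is not shown. It is still a gap in the published definitions.

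**Conclusion.** The concern holds in this form: the selection rule conflicts with the stated aim of controlling confounding, and the data cannot support selection among this many parameters. Within 96 to 120 patients there are at most about 3 to 4 events per candidate parameter, and far below one at the low cited rates. Under the assumed effects, loss of a true confounder is likely. Intervals may under-cover, mildly with the exposure kept in (90 to 94%) and more seriously when Modic type 1 is itself selected (81 to 87% at true odds ratio 2, N = 96), with the estimate nearly doubled. With only 2 to 4 colonized patients the asymptotic interval may not exist.

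This affects the association with the clinical and radiological profile. The documents do not support extending it to the primary outcome: the incidence of colonization is a simple proportion and does not pass through this model. The change should be made, but it does not threaten the study's main result.

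**What to change.** Delete forward Wald selection for the association models. Keep the exposure of interest (for example Modic type 1) in the model with a short confounder set, chosen on subject-matter grounds and fixed before colonization results are seen. Scale the number of parameters to the colonized count. As an illustration only, 44 events allow about 4 parameters at an assumed 10 events each (44 / 10) and about 8 at an assumed 5 (44 / 5); all 15 at 10 each would need 150 colonized patients, or about 326 participants at 46% (150 / 0.46). The documents give no basis for naming the variables or a cut-off, so the investigators must set and justify both.

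When events are sparse, use Firth-penalised logistic regression with profile-likelihood intervals, and exact or mid-p intervals for odds ratios from 2 × 2 tables. Where there are too few events to adjust at all, report only unadjusted exact results and say so.

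Add an intermediate physical-activity category between Sedentary and Active, and check that the collection form has it.

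The cost is a few sentences of analysis text and, if needed, one category on the form. The downside is somewhat wider intervals and fewer covariates adjusted for.
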